### 3.2.2 Two weeks rule for scheduled visits

A window of 2 weeks before or after the scheduled visit date will be considered for V2, V3, V4 and V5. For example, a woman coming to the clinic for a follow-up visit two weeks earlier (or later) than the expected scheduled date at 9 months postnatal will be assigned V3. This rule applies for both regular quarterly visits (V1, V2, V3, V4, V5) and the test of cure visits (V1.9, V2.9, V3.9, V4.9).

### 3.2.3 Women seen after the window of 2 weeks (Missed Visits)

For women seen after the window of 2 weeks, complete a missed visit form and assign the missed visit # on the form. **However, the test of cure visit (1.9, 2.9, 3.9 and 4.9) cannot be missed.** If a woman has missed her test of cure visit (taking into account  $\pm 2$  weeks of the scheduled date), a missed visit form with all other forms to be completed at a regular test of cure visit should be completed,

and vaginal samples should also be collected. Specifically, the following should be done: A) complete Missed Visit Form, B) complete Acceptability History Form, C) Complete Product Monitoring and Genital History Form, C) Collect Vaginal mount and smear (for Gram stain), and do urine pregnancy testing.

**Important Note:** If the client presents at a time when she is due for her regular visit after missing the test of cure visit, all the above procedures should be done (from A to C) and the visit # should be that of the missed visit (e.g., 2.9 or 3.9). In addition, complete regular visit forms and collect other specimens such as STD samples and blood - on these forms indicate the regular visit number (not the missed visit number).

**Example of a missed quarterly visit and of a missed test of cure visit:**

1. Client comes for V1 on January 1 and V1.9 on February 1; then skips V2 on April 1 and does not return until May 15. This client should be re-scheduled for V3 on July 1. A missed visit 2 form should be completed. **Because this client came for the test of cure visit, we will only document that V2 was missed (remember that by missing V2 this client did not receive product and therefore we will not complete a product monitoring or acceptability/genital history forms, and will not collect samples). We are re-scheduling this client to a regular visit on July 1 to avoid irregularities with scheduling (i.e., if we consider this as a regular visit, all future visits will be changed).**

2. Client above skips the test of cure visit on February 1 and returns for her V2 on April 1. As we explained above a test of cure cannot be missed; **therefore complete the Acceptability Form, Product Monitoring/Genital History Form, and collect vaginal samples. These forms should be coded as V1.9. In addition, complete all other follow-up study forms and collect all other laboratory samples; code these forms as V2.**

3.2.4 **Unscheduled visits**

Unscheduled visits will be identified by visit date in addition to the usual identifiers such as ID number.

3.3 **Clinic ID code**

Each participating clinic including QECH will have an identification code. This code will appear on all forms and local laboratory specimens. In the METRO study the clinic codes are as follows:

|            |   |
|------------|---|
| QECH       | 1 |
| Limbe      | 2 |
| Cholomoni  | 3 |
| Zingwangwa | 6 |
| Ndirande   | 7 |

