All women will be tested for disturbance of vaginal flora and syphilis at the first visit (3 months postnatally) and at each subsequent visit. To determine if this treatment reduces *T. vaginalis* infection, vaginal wet mounts obtained from all women (HIV negative and positive) will be examined at each visit. Urine samples will be tested at 6, 9 and 12 months postnatal visits to confirm conception and estimate rates of early pregnancy loss. Information on the last menstrual period (LMP) and history of bleeding (or spotting) will also be collected at each visit. Abortions and stillbirths will be observed and documented throughout the follow-up period. For the secondary objective (to determine clinical and behavioral factors which facilitate or impede the long-term use of metronidazole vaginal gel in a community where use of traditional vaginal agents is common) qualitative and quantitative clinical and behavioral data will be longitudinally collected postnatally to compare side-effects, compliance and acceptability between women who use the active product or the placebo. The information collected at each visit will pertain to events occurring during the past three months; i.e., most recent events. HIV negative women will be tested to confirm HIV seroconversion. HIV serology will be performed on the same blood sample which is used for syphilis testing.

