#### 12.3.1 Instructions for using the allocation study ID's

##### By Whom

Study coordinator (as the rest of the study investigators and workers, the study coordinator is completely blinded about the treatment assignment).

Procedure

1. Assign these Lists to the five Study Clinics as shown in section 12.3. above
2. Each woman enrolling in the study will be sequentially assigned the next available ID in each clinic.

12.4 Sample size and analysis plan12.4.1 Sample size and power:

The following design specifications will apply: number of treatment groups: 2; follow-up period: approximately one year; hypotheses will be tested using a one-sided type 1 error of  $\alpha=0.05$ . Unless stated otherwise, powers are obtained based on Fisher's exact test for comparisons of proportions in two groups.

We will recruit 1664 women of whom 832 will be HIV infected and 832 will be uninfected. In each group of women, 416 will be randomized to treatment arm and 416 to placebo arm. Based on previous experience in Malawi, losses due to dropouts and non-compliance will be less than 10% per year. Thus at least 375 women in each arm will return to each study visit during the first year.

Primary endpoint: effect of treatment on BV incidence. Power estimates for this primary endpoint are shown in Tables 12.1. In previous studies from Malawi, cross sectional prevalence of BV among untreated women was 30% and that of any vaginal disturbance was 89%.

**Table 12.1. Estimated power for specific aim 1 (comparing BV at each visit during the first study year assuming at least 375 evaluable study subjects in each group).**

| Normative rate
in untreated women | Reduction from intervention |       |
|--------------------------------------|------------------------------------|-------|
|                                      | 33%                                | 50%   |
| 0.30                                 | .87                         | ~1.00 |
| 0.89                                 | ~1.00                       | ~1.00 |

Thus there will be **0.87** and almost **1.00** power to detect 33% reductions in cross sectional visit prevalence of BV (normative rate 0.30 in untreated subjects) and any vaginal flora disturbance (normative rate .89 in untreated subjects).

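### A woman who kept her test of cure visit but attends a quarterly visit more than 2 weeks late has no samples taken, so an obtainable BV reading and pregnancy test are forgone

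*Protocol*

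**What the plan says.** Section 3.2.2 sets the visit window: "A window of 2 weeks before or after the scheduled visit date will be considered for V2, V3, V4 and V5". Section 3.2.3 then says what happens outside it: "For women seen after the window of 2 weeks, complete a missed visit form and assign the missed visit # on the form".

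Example 1 under that section applies the rule. "Client comes for V1 on January 1 and V1.9 on February 1"; she "then skips V2 on April 1 and does not return until May 15". Because she kept her test of cure visit, staff only document that V2 was missed. She received no V2 product, and "therefore we will not complete a product monitoring or acceptability/genital history forms, and will not collect samples". She is booked for V3 on July 1, on the ground that counting May 15 as a regular visit would shift all later visits.

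For the one-month visits section 3.2.3 says the reverse: "However, the test of cure visit (1.9, 2.9, 3.9 and 4.9) cannot be missed". When one is late, the forms, wet mount, smear and urine pregnancy test are still done and coded to the missed visit.

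Three other places bear on this. Section 12.2.1 makes BV at cross-sectional visits, the conception rate and pregnancy loss within 14 weeks primary endpoints. Section 12.6 specifies intention to treat and a GEE analysis pooling BV over all post-intervention visits. Section D.1 limits the histories: "The information collected at each visit will pertain to events occurring during the past three months; i.e., most recent events".

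**The concern.** The woman is in the clinic, the tests are already part of the schedule, and the outcomes are primary. Neither stated reason supports leaving them out.

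- **No product was issued at V2.** V2 samples show the flora after the V1 course. Whether she later received the V2 tube does not affect what they measure, and intention to treat needs the outcome whatever product was received.
- **The calendar would shift.** A dated sample on May 15 does not move July 1. Section 3.2.4 already identifies unscheduled visits by date.

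The result is also perverse. A woman who kept her test of cure visit gets no sample when she comes late for the quarterly visit. A woman who missed the test of cure visit is sampled when she next appears.

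At stake are missing primary data created by the rule and not only by the woman's absence. Late attendance may be related to illness, pregnancy or mobility. If it is, the missing results are informative, and no analysis can recover a sample that was not taken.

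**Working it through.** **Inputs.** Dates from example 1: V1 January 1, V1.9 February 1, V2 due April 1, attendance May 15, V3 July 1. Window: 14 days either side (3.2.2). Loss endpoint: 14 weeks = 98 days (12.2.1). Urine pregnancy tests are scheduled at every quarterly and test of cure visit (3.2). Sample size: "Thus at least 375 women in each arm will return to each study visit during the first year" (12.4.1).

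**1. Lateness.** April 1 to May 15 = 44 days, more than 14, so the rule applies.

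**2. Interval between pregnancy tests** (non-leap year; a leap year adds one day to intervals that span the end of February).

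| Situation | Test dates | Longest interval |
|---|---|---|
| On schedule | Feb 1, Apr 1, about May 1 (V2.9), Jul 1 | about 2 months (59 to 61 days) |
| Rule as written | Feb 1, Jul 1 | 150 days |
| Sampled on May 15 | Feb 1, May 15, Jul 1 | 103 days (then 47) |

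103 + 47 = 150. The interval under the rule exceeds 98 days by 52; with sampling it exceeds 98 by 5.

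**3. BV readings.** After baseline there are eight: V1.9, V2, V2.9, V3, V3.9, V4, V4.9 and V5. In the example V2 and V2.9 are both absent. V2.9 is absent because it follows product issued at V2 and none was issued. Only the V2 reading, one of eight, is lost through not sampling on May 15.

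**4. Recall.** A three-month history on July 1 reaches back to April 1. The genital history form completed at V1.9 on February 1 covers January. Read literally, February 1 to April 1 (59 days) falls outside both.

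**5. Power of the per-visit BV comparison.** The document states 0.87 for 375 per arm. Exact Fisher power is the sum, over all pairs of binomial counts, of the probability of those pairs whose hypergeometric tail probability is at most alpha. With 0.30 against 0.20 and n = 375 it gives 0.872 at one-sided 0.025 (the final-analysis level under Data monitoring in D.4) and 0.926 at one-sided 0.05 (the level in 12.4.1). The stated figure therefore matches the 0.025 level; that mismatch is a separate matter.

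The share attending late is not given. Assumed shares taken off 375:

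| Late share (assumed) | n per arm | One-sided 0.05 | One-sided 0.025 |
|---|---|---|---|
| 0% | 375 | 0.926 | 0.872 |
| 5% | 356 | 0.914 | 0.853 |
| 10% | 337 | 0.900 | 0.832 |
| 15% | 318 | 0.883 | 0.810 |

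These overstate the effect if some late visits already fall within the loss allowance, since 416 × 0.90 = 374.4 is where 375 comes from.

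**The case against.** The strongest reply is that the rule is narrow and most of the gap is the woman's own absence. Of the 150 days, 103 pass before she appears. That stands: sampling her shortens the gap but does not bring it under 98 days, so a conception and its loss could still go unseen. Very early losses can also fall between tests on the planned schedule.

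A second reply is that a fixed-time prevalence may properly exclude out-of-window readings. Section D.3.a reports recurrence of 10%-15% by one month and 50%-70% after 3 months, so a reading about four and a half months after V1 is not exchangeable with one at 3 months. This also stands. It is a reason to keep late readings out of the per-visit comparison. It is not a reason to leave them uncollected, because the pooled analysis and pregnancy ascertainment can use them by date.

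A reader might infer more than the text supports:

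- **That late quarterly visits are never sampled.** The instruction is written for a woman who kept the preceding test of cure visit; one who missed it is sampled under 3.2.3.
- **That data are thrown away.** Nothing collected is discarded; the data are not gathered.
- **That each late visit costs two BV readings.** V2.9 is lost because no V2 tube was issued, and sampling on May 15 would not restore it.
- **That everything between V1 and April 1 goes unasked.** The V1.9 form covers January. Menstrual and bleeding history is taken at each visit, and abortions and stillbirths are documented throughout (D.1). The exact questions are in an appendix not shown.
- **That power falls short.** At the 0.05 level in 12.4.1, every assumed case above stays over the stated 0.87.

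**Conclusion.** The point holds in a limited form. For a woman who kept the preceding test of cure visit and attends a quarterly visit more than 2 weeks late, the protocol forgoes one BV reading and one pregnancy test that could be taken that day, for reasons that do not justify it under intention to treat. In the protocol's own example this leaves 150 days between pregnancy tests where 103 was achievable.

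The supported harm is avoidable and possibly informative missing data on primary endpoints. A power shortfall is not shown. How often the rule would operate is unknown, and the document gives nothing to show that late attendance differs by arm. That late attenders differ from punctual ones is plausible but assumed. This is a worthwhile, low-cost improvement and not a defect that undermines the trial. It has to be made while follow-up is running, because the samples cannot be obtained afterwards.

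**What to change.** Amend section 3.2.3 and example 1:

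1. When a woman attends after the quarterly window, do that visit's wet mount, Gram-stain smear, urine pregnancy test and follow-up history on the day. Record them as a late visit with the actual date, and keep the next visit on its calendar date.
2. Use these results by actual date in the pooled GEE analysis of BV and in pregnancy ascertainment. Keep the per-visit BV comparison to in-window readings, and add an in-window-only sensitivity analysis of the pooled result.
3. Let the history cover the time since the last attended visit, not only the past three months.

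The cost is a manual addendum, a change to the recall period on the forms, and already planned tests on women who are already present. The downside is some off-schedule BV readings, handled by steps 1 and 2. The change does not restore V2.9 or the per-visit sample size. Whether product is issued at a late visit is a clinical rule and is not addressed here.

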### D. 3. STUDY PRODUCT

**D. 3. a. Active product.** We will use metronidazole vaginal gel, 0.75% MetroGel-Vaginal (3M Pharmaceuticals) in this study. Based on a Clinical Monograph from the company (55), “MetroGel-Vaginal is an effective, well-tolerated local treatment for BV. Each gram of MetroGel-Vaginal contains 7.5 mg of metronidazole, 0.8 mg of methyparaben, 0.2 mg of propyl-paraben in an exclusive hydrogel vehicle consisting of purified water, propylene glycol, carbomer 934P, sodium hydroxide (to adjust pH), and edetate disodium. The gel is buffered to a normal pH of 4.0 and is free of mineral oil. Each applicatorful delivers about 5 grams of gel and contains approximately 37.5 mg of metronidazole in solution, thus, the pharmacologic activity of metronidazole is not limited by drug dissolution.”

The product is used intravaginally either once (at bedtime) or twice a day. Both regimens have comparable efficacy (1). Clinical trials which compared intravaginal gel (5 gm BID for 5 days) vs oral metronidazole (500 mg BID for 7 days) have also shown comparable efficacy of about 84% after 11-17 days from start of therapy to 71% after 34-40 days from initiation of therapy (55). Despite its wide spread use, metronidazole is reported to be highly active and drug resistance is relatively rare (55). This is a desirable feature since we intend to use this drug intermittently for a longer period. Metro-Gel is reported to increase vaginal lactobacilli (55). We anticipate longer treatment to reduce recurrences and help to restore normal vaginal flora. It is estimated that 10%-15% of women who initially respond to therapy, relapse by one month after treatment, and 50%-70% of women develop recurrences after 3 months of initial therapy (1). Several causes have been postulated to account for these recurrences (1); for example, inability to reestablish normal *lactobacillus*-dominant protective flora, persistence of BV-causing bacteria and reinfection by a male partner.

**D. 3. b. Placebo.** The placebo will be manufactured to be similar to the active product but without the active ingredient. Identical consistency, color, smell and packaging will be maintained.

**D.3. c. Provision of MetroGel and placebo.** We have discussed this protocol with 3M Pharmaceuticals and the company has agreed to donate the treatment and the placebo for this study (see Appendix: letter from 3M Pharmaceuticals).

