### 3.2.1 Visit numbering

The METRO study will use a sequential visit numbering starting from V1 as shown below.

**Please note:** The first METRO study visit starts postnatally at 3 months; this will represent V 1. Each quarterly visit is followed by a test of cure visit one month after using the product; these one month follow-up visits are coded as 1.9, 2.9, 3.9, 4.9 (NO V 5.9 because no product is used at V5). The purpose of test of cure visits is to collect vaginal samples to determine if there has been changes in vaginal flora following use of the study product. We will also complete Acceptability and Product Monitoring forms at these visits.

The METRO study visit numbers are as follows:

**V 1:** Visit at 3 months postnatal; followed by a test of cure visit after one month (i.e., at 4 months postnatal) - ***this visit is coded V1.9.***

**V 2:** Visit at 6 months postnatal; followed by a test of cure visit after one month (i.e., at 7 months postnatal) - ***this visit is coded V2.9***

**V 3:** Visit at 9 months postnatal; followed by a test of cure visit after one month (i.e., at 10 months postnatal) - ***this visit is coded V3.9.***

**V 4:** Visit at 12 months postnatal; followed by a test of cure visit after one month (i.e., at 13 months postnatal) - ***this visit is coded V4.9.***

**V 5:** Visit at 15 months postnatal. This is the last follow-up visit (remember that the test of cure visit should occur one month after V4 when the last tube is issued).

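### Samples taken at a quarterly visit are coded as the missed one-month test-of-cure visit, so they carry the wrong time label and leave that quarter's BV result either absent or entered twice

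*Protocol*

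**What the plan says.** The manual of operations places the test-of-cure visit at a fixed time: "Each quarterly visit is followed by a test of cure visit one month after using the product" (Section 3.2.1). Its purpose is to "collect vaginal samples to determine if there has been changes in vaginal flora following use of the study product". Section 3.2.2 allows two weeks either side and includes these visits: "This rule applies for both regular quarterly visits (V1, V2, V3, V4, V5) and the test of cure visits".

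Section 3.2.3 then states that a test-of-cure visit cannot be missed. A woman who did not come is to have the vaginal mount, the smear for Gram stain and a urine pregnancy test when she next appears. If that is when her regular visit is due, all these procedures are done "and the visit # should be that of the missed visit (e.g., 2.9 or 3.9". The regular number goes on the regular forms and on other specimens such as STD samples and blood.

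The second worked example applies the rule. V1 is on January 1, the test of cure due on February 1 is skipped, and the woman returns on April 1, when V2 is due. Staff complete the acceptability and product-monitoring forms "and collect vaginal samples. These forms should be coded as V1.9". The other follow-up forms and all other laboratory samples are coded V2. No separate V2 vaginal sample is mentioned.

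The schedule in Section 3.2 requires BV testing at every quarterly visit. Section 12.2.1 lists BV at cross-sectional visits as a primary endpoint, and Section 12.6 pools BV over all post-intervention visits in a GEE model.

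**The concern.** The visit number is the time label of the result. Under this rule a sample taken at three months is stored as a one-month result, against Sections 3.2.1 and 3.2.2 of the same manual.

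The rule also affects the quarterly result. If the vaginal sample belongs to V1.9 and only the other samples belong to V2, the V2 comparison has no BV value for that woman. If staff reuse the specimen or take a second one the same day, a single day's flora appears as two visits. The text does not say which is meant.

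The rule covers V1.9 to V4.9, so the final BV result at V5 can be filed as V4.9. By Section 3.2.3 it also covers the urine pregnancy test, so a pregnancy found at V2 could be labelled about two months early, and rate of conception is part of a primary endpoint. The example does not name the urine test and would leave it among the samples coded V2, so the two places also need to be aligned on this.

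**Working it through.** **Dates (second example, Section 3.2.3).**
- V1.9 is due February 1. The window of two weeks either side runs from January 18 to February 15.
- The sample is taken April 1. That is 90 days after January 1, 59 days after the due date and 45 days after the window closed.
- The V2 window, two weeks either side of April 1, runs from March 18 to April 15. The sample is exactly on the V2 date.

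**Do the two times differ?** Research plan Section D.3.a gives 10%-15% relapse by one month among women who initially respond, and "50%-70% of women develop recurrences after 3 months of initial therapy".

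**Size of the mixing.** The plan gives no figure for this, so there is none to reproduce. Let m be the share of V1.9 results that are really three-month samples. The documents do not give m, so 5% to 30% is assumed. Both rates are read as applying to treated women who initially responded. With r1 = 0.10 to 0.15 and r3 = 0.50 to 0.70:

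recorded V1.9 relapse = (1 - m) × r1 + m × r3

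| m (assumed) | Low inputs | High inputs |
|---|---|---|
| 0 | 0.10 | 0.15 |
| 5% | 0.95×0.10 + 0.05×0.50 = 0.12 | 0.95×0.15 + 0.05×0.70 = 0.18 |
| 10% | 0.90×0.10 + 0.10×0.50 = 0.14 | 0.90×0.15 + 0.10×0.70 = 0.205 |
| 20% | 0.80×0.10 + 0.20×0.50 = 0.18 | 0.80×0.15 + 0.20×0.70 = 0.26 |
| 30% | 0.70×0.10 + 0.30×0.50 = 0.22 | 0.70×0.15 + 0.30×0.70 = 0.315 |

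At m = 10% the shift is 4.0 to 5.5 percentage points among responders. Treatment is given to all women, and the planning prevalence of BV is 30% (Section 12.4.1). If every woman with BV responded, the shift across the whole active arm from this source would be 0.30 × 4.0 = 1.2 to 0.30 × 5.5 = 1.65 points. The protocol gives no matching figures for placebo, so the effect on the treatment contrast cannot be computed.

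**If the V2 result is treated as absent.** Section 12.4.1 plans 375 evaluable women per arm and states power .87 for 0.30 against a 33% reduction (0.201). Exact one-sided Fisher power at 375 per arm is 0.865 at level 0.025 and 0.92 at the stated level 0.05. The stated figure therefore reproduces only at 0.025, which is a separate matter. Losing a share m of V2 results gives:

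| m (assumed) | n per arm | Level 0.025 | Level 0.05 |
|---|---|---|---|
| 0 | 375 | 0.865 | 0.92 |
| 10% | 338 | 0.825 | 0.895 |
| 20% | 300 | 0.775 | 0.86 |
| 30% | 262 | 0.715 | 0.81 |

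**If the specimen counts twice.** The GEE clusters on the woman with robust covariance, so the variance allows for the correlation. The extra weight on that day's result and the wrong time label on one of the two entries remain.

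**The case against.** The strongest reply is that Section 3.2.3 governs forms, not analysis sets. Source-document entries must be dated (Section 10.3) and a Missed Visit Form is required, so late samples can be found. Assigning results to time windows by date is commonly left to a statistical analysis plan. A single sample labelled V1.9 still enters the pooled model once. The schedule, and the human-subjects section on research material, call for vaginal samples at every visit, so a V2 swab may be intended.

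Much of this stands. The records are recoverable, and loss and duplication are alternative readings, not both certain. It does not remove the contradiction: the manual sets a window for these visits and then tells staff to apply the number outside it, with no step to reassign by date.

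Three stronger readings are tempting but not supported.
- A reader might infer that a cure endpoint is corrupted. Sections 12.2.1 and 12.2.2 list none. The harm runs through BV by visit and pooled BV.
- A reader might infer bias that differs by arm because attendance follows symptoms. Nothing in the documents shows this in a double-masked trial.
- A reader might add the first example, where a woman who comes on May 15 for V2 is rescheduled and staff "and will not collect samples". May 15 is 44 days after V2 and 47 days before V3, outside both windows. The manual gives its reason, which is to keep the schedule fixed. That is a trade-off and does not contradict intention to treat.

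**Conclusion.** The concern holds as a coding error in the manual. Sections 3.2.1 and 3.2.2 define the test-of-cure visit as one month after product, give or take two weeks. Section 3.2.3 and its second example give that label to a sample taken at about three months. As worded, the quarterly BV result, part of a primary endpoint, is then absent under its own visit number or entered as two visits.

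The size is illustrative, because the share misfiled is not given. Section 12.4.1 expects losses and non-compliance below 10% a year but says nothing specific about test-of-cure attendance, so the rows for 20% and 30% are a range and not a forecast. At an assumed 10%, recorded V1.9 relapse among treated responders would be about 14-21% instead of 10-15%. This assumes that the relapse and recurrence figures in Section D.3.a apply to this gel regimen and this population. The power figures apply only if the V2 result is treated as absent and not recovered from its date.

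**What to change.** Amend Section 3.2.3 and the second example as follows.
- Code vaginal and urine samples by the actual date. A sample taken within the quarterly window is coded as that quarterly visit and used once.
- If no sample was taken within the test-of-cure window, set that test-of-cure flora result to missing and complete the Missed Visit Form.
- Keep the acceptability and product-monitoring forms as late test-of-cure forms with their true dates.
- Make Section 3.2.3 and the example agree on the urine pregnancy test.
- Recode existing records from the visit dates and Missed Visit Forms, and look for same-day results held under two visit numbers.

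The cost is a change of wording, a note to clinic staff and one pass through recorded dates. No new type of procedure is needed. The downside is fewer test-of-cure results, but those set to missing were not one-month results.
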